##### *Exclusion criteria:*

- 1) Primary immunodeficiency for which intravenous immunoglobulin (IVIG) treatment has started,
- 2) Secondary immunodeficiencies (e.g. HIV, chemotherapy, transplantation),
- 3) Major congenital anomalies (eponymous syndromes, chromosomal abnormalities, cleft palate, renal or hepatic insufficiency, known glucose-6-phosphate deficiency, cystic fibrosis, primary ciliary dyskinesia or acute porphyria),
- 4) Antibiotic use (prophylactic or course) four weeks prior to inclusion (if this is the only exclusion criteria, a child can be included but a mucosal sample should be collected four weeks after the last antibiotic course or prophylactic treatment). Furthermore, subjects with azithromycin prophylaxis three months prior to sampling are also excluded, since this could influence *M. pneumoniae* carriage,
- 5) Both parents below the age of 18 years,
- 6) Language barrier that prevents a proper informed consent procedure,
- 7) No informed consent.

#### ***Controls:***

##### *Inclusion criteria:*

Family members of children with rRTIs included in the DIMER study, living in the same household (for most of the time). A family member does not need to be a biological family member if they live in the same household as the patient with rRTIs. Multiple controls can be included per child with rRTIs.

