### **Brief description of DIMER-Mycoplasma sub-study**

The DIMER study is a cohort study including children between six weeks and eight years with recurrent respiratory tract infections (rRTIs) and their family members. One of the primary aims is to compare the prevalence of primary antibody deficiencies and *Mycoplasma pneumoniae* carriage in children with rRTIs to controls without infections. In addition, we aim to investigate the mucosal immune system, including differences in mucosal antibody levels and the nasopharyngeal microbiota composition, in children with rRTIs with and without *M. pneumoniae* carriage.

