#### **Objectives**

1. To provide an overview of the prevalence of *M. pneumoniae* carriage in young children with rRTIs and compare this to their family members without infections.
2. To investigate mucosal and systemic immune factors, including (specific) mucosal antibody levels and the local respiratory microbiota, in relation to *M. pneumoniae* carriage in young children with rRTIs.

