#### ***Controls (family members of children with rRTIs)***

After the inclusion of a subject with rRTIs, family members will be asked to participate in the study if they fulfill the in- and exclusion criteria. Again, information about the study is supplied beforehand and the informed consent procedure will take place prior to sample and data collection as described above. For young siblings, a blood draw can also take place via a finger prick if this is the caretakers' wish.

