### **Statistical analyses**

All clinical and laboratory data will be combined in a single dataset. Microbiota data measured with 16S-rRNA sequencing will be filtered and annotated through standardized methods from our study group and stored as a separate file. All analyses will be conducted using R and R Studio.

Baseline characteristics will be compared with Chi-square/Fishers exact test and Mann-Whitney U test. Correlations will be identified using Pearson's/Spearman's correlation test. Where appropriate, analyses will be corrected for age as a possible confounding variable. *M. pneumoniae* carrier status will be compared with univariable and multivariable logistic regression analysis (using the Akaike Information Criterion comparing the fit of subsequent models).

For the microbiota data, alpha diversity will be measured using the Shannon index and beta diversity will be based on the Bray-Curtis dissimilarity matrix. All further microbiota analyses will be based on total sum scaled (relative) abundances.

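### Controls share households with the index children, but the methods named for child-versus-family comparisons assume independent subjects and carry no household term

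*Protocol*

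**What the plan says.** - **Source of controls.** Under the inclusion criteria for controls (Protocol, Study subjects), a control must live in the home of an enrolled child with recurrent respiratory tract infections. The section adds: "Multiple controls can be included per child with rRTIs". No maximum is set. Recruitment runs through the child: "After the inclusion of a subject with rRTIs, family members will be asked to participate in the study" (Workflow, Controls).
- **The comparison.** Objective 1 is to describe M. pneumoniae "carriage in young children with rRTIs and compare this to their family members without infections". The Brief description gives it high standing: "One of the primary aims is to compare the prevalence of primary antibody deficiencies and" M. pneumoniae carriage against controls.
- **The analysis.** Under Statistical analyses, M. pneumoniae "carrier status will be compared with univariable and multivariable logistic regression analysis", with successive models compared by AIC. The same section says: "Baseline characteristics will be compared with Chi-square/Fishers exact test and Mann-Whitney U test". The only adjustment named is age: "Where appropriate, analyses will be corrected for age as a possible confounding variable". Household, pairing, matching, random effects and robust variance do not appear.

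**The concern.** The design links each control to an index child and may link several controls to each other. M. pneumoniae is a respiratory pathogen, and people in one home share exposure and often genes, so some within-household correlation of carriage is to be expected. Logistic regression, chi-square, Fisher and Mann-Whitney tests, as named, treat all subjects as independent.

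Two effects then pull in opposite directions. Correlation between a child and its own controls makes the true variance of the difference smaller than the independence formula says. Correlation among controls from one home makes it larger. Which one wins depends on how many children bring controls and how many each brings. AIC is computed from the same independence likelihood, so the choice of covariates is affected as well whenever controls are in the model. What is at stake is the precision, and possibly the conclusion, of a comparison listed among the primary aims.

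**Working it through.** The protocol states no sample size, significance level, carriage rate, number of controls per child or household correlation. There is therefore no figure of its own to reproduce, and every input below is an assumption.

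**Inputs.** N index children; a share f of them bring m controls each; within-household correlation rho, equal for all pairs; equal carriage in both groups (the null); nominal two-sided 5% test; no covariates.

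**Variance of the difference in prevalence**, in units of s²/N:
- Independence formula: 1 + 1/(fm)
- True: 1 + [1 + (m−1)rho]/(fm) − 2rho
- Actual type I error = 2 × [1 − Φ(1.96/√ratio)], where ratio = true/independence variance.

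**Direction.** True minus independence variance is rho × [(m−1)/(fm) − 2]. The independence standard error is too small only if f < (m−1)/(2m): f below 0.25 for m=2, 0.33 for m=3 and 0.375 for m=4. For m=1 it is never too small.

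**Case A: every child brings m controls (f=1).** The true variance reduces to (1 + 1/m)(1 − rho), so the ratio is 1 − rho for any m.

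| rho | Ratio | Actual type I error |
|---|---|---|
| 0.1 | 0.9 | 3.9% |
| 0.2 | 0.8 | 2.8% |
| 0.3 | 0.7 | 1.9% |
| 0.5 | 0.5 | 0.6% |

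At rho=0.3 the independence standard error is 1/√0.7 = 1.195 times the true one, and 1 − 0.7 = 30% of the information is lost. A simulation with 200 households, 10% carriage and 20,000 runs agrees: 1.9% at m=2, rho=0.3, and 3.9% at m=3, rho=0.1.

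**Case B: few children bring many controls (f=0.3, m=4, so fm=1.2).** Independence variance: 1 + 1/1.2 = 1.833.
- rho=0.3: true variance 1 + 1.9/1.2 − 0.6 = 1.983; ratio 1.082; standard error about 4% too small; type I error 6.0%.
- rho=0.5: true variance 1 + 2.5/1.2 − 1 = 2.083; ratio 1.136; type I error 6.6%.

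**Case C: unequal correlations (f=1).** Let r1 be the child-control and r2 the control-control correlation. The true variance is 1 + [1 + (m−1)r2]/m − 2r1. For r1 = 0 to 0.05, r2 = 0.3 to 0.5 and m = 2 to 3, the type I error is 5.4% to 8.0%. The terms can also cancel: with m=3, r1=0.1, r2=0.3, the true variance is 1 + 1.6/3 − 0.2 = 1.333, the same as 1 + 1/3.

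**Control prevalence alone.** The design effect is 1 + (m−1)rho. At rho=0.3 the standard error is understated by √1.6 = 1.26 for m=3 and √1.9 = 1.38 for m=4. For m = 2 to 3 and rho = 0.1 to 0.5 the design effect is 1.1 to 2.0, and a nominal 95% interval covers about 94% down to 83%. At m=1 there is no understatement.

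**The case against.** The best defence is that the protocol says logistic regression without saying ordinary. Conditional, mixed or GEE logistic models would fit the wording, and variance estimation is often left to a statistical analysis plan, which is not at hand. It is true that the wording does not exclude a clustered model. But the section specifies its tests, its model-selection criterion and its one named confounder, does not refer to a later plan, and leaves out the feature that the control design creates. Followed as written, it gives an independence analysis.

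Several stronger readings are tempting, and the document does not support them:
- **That every planned test is affected.** Objective 2 and the microbiota and antibody comparisons by carriage concern children with recurrent infections only. Those analyses are largely untouched, unless siblings are both index cases.
- **That chi-square is the carriage test.** The section assigns chi-square, Fisher and Mann-Whitney to baseline characteristics. They matter here only where baseline is compared between children and family members.
- **That false positives are inflated.** In Case A the test is conservative. Inflation needs few children with many controls, or controls that resemble each other much more than they resemble the child.
- **That the control prevalence interval is always too narrow.** This needs two or more controls from at least some homes, which the protocol permits but does not require. Nor does the protocol mention such an interval, a significance level or p-values.

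It also stands that the size of the error is wholly assumed and in many scenarios modest.

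**Conclusion.** The point holds for child-versus-family comparisons. The design is clustered by household, and the methods named for those comparisons, including AIC selection, assume independence. They are right only if within-household correlation is zero or the two covariance effects happen to cancel.

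The likelier consequence, if most children bring controls and correlations are similar within a home, is standard errors that are too large and a loss of power (about 1.9% actual error and 30% of the information lost at rho=0.3). If few children bring many controls, the test is slightly liberal (about 6.0% to 6.6%). Where homes supply two or more positively correlated controls, an interval for control prevalence is too narrow. Neither direction nor size can be derived from the protocol, since both depend on the assumed correlation and number of controls per child.

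**What to change.** In Statistical analyses, for child-versus-family comparisons only:
- Name one primary household-clustered analysis of carriage. One choice is an age-adjusted logistic GEE with household as cluster and robust variance, with QIC in place of AIC because GEE has no full likelihood. The other is a random-intercept logistic model, for which AIC can stay.
- Add conditional logistic regression stratified by household as a sensitivity analysis, and note that it drops households in which all members have the same carriage status.
- Use household-clustered methods for the other measures compared between children and family members.
- Keep the simple tests and plain logistic regression for comparisons among index children (objective 2).

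Two additions should be avoided. The interval from the index child's swab should not be a covariate, because it is zero for every index child and so tied to the group being tested. A GEE result should not be described as a within-household contrast, because it is population-averaged.

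The cost is a few sentences, a little more analysis work and possibly wider intervals for control prevalence. No new measurements are needed. The dataset must carry a household identifier; recruitment through the index child makes this readily available, although Data storage mentions only individual pseudo-IDs.

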##### *Exclusion criteria:*

- 1) Known immunodeficiencies (except IgA deficiency),
- 2) Recurrent respiratory tract infections,
- 3) Secondary immunodeficiencies,
- 4) Major congenital anomalies,
- 5) Antibiotic use (prophylactic or course) four weeks prior to inclusion (if this is the only exclusion criteria, a family member can be included but a mucosal sample should be collected four weeks after the last antibiotic course or prophylactic treatment).

Furthermore, subjects with azithromycin prophylaxis three months prior to sampling are also excluded, since this could influence *M. pneumoniae* carriage,

- 6) In the case of a sibling below the age of 16 years: both parents below the age of 18 years,
- 7) Language barrier that prevents a proper informed consent procedure,
- 8) No informed consent.

### **Workflow identifying potential study subjects and providing study information**

#### ***Children with recurrent respiratory tract infections:***

New patients that may fulfill the inclusion criteria of the study will be identified from the outpatient clinic by the treating physician and/or a member of the study team. Caretakers of patients will be called one to two weeks in advance and receive oral and written information from the study team.

During the outpatient clinic visit, the treating physician will decide whether an immunological screening is appropriate and inform the study team. If a patient is indeed a candidate (after checking the in- and exclusion criteria), the informed consent will be signed by caretakers and a member of the study team prior to a blood draw, mucosal sample collection, and filling in the inclusion questionnaire. A mucosal sample will only be collected if there is no antibiotic use in the previous four weeks. Later sampling (after a period of four weeks without antibiotic use) can occur during a home visit if no further hospital visits are planned.

#### ***Controls (family members of children with rRTIs)***

After the inclusion of a subject with rRTIs, family members will be asked to participate in the study if they fulfill the in- and exclusion criteria. Again, information about the study is supplied beforehand and the informed consent procedure will take place prior to sample and data collection as described above. For young siblings, a blood draw can also take place via a finger prick if this is the caretakers' wish.

### **Sampling**

#### Collection of samples

#### ***Children with recurrent respiratory tract infections:***

Mucosal samples: nasopharyngeal swab, saliva, and feces.

Blood samples: serum, plasma, EDTA, and PBMC's. Blood will only be collected from children with rRTIs when there is a clinical indication for blood drawing.

#### ***Family members***

Mucosal samples: nasopharyngeal swab, saliva, and feces.

Blood samples: serum, plasma, EDTA, and PBMC's. Blood collection will only take place once.

#### Timing of sampling

- In subjects without antibiotic use in the previous four weeks: all samples, including blood, will be collected at inclusion.
- In subjects with antibiotic use in the previous four weeks and in whom a pneumococcal vaccine response will be measured in 4-6 weeks: all samples, including blood, will be collected when pneumococcal response is measured.

- In subjects with antibiotic use in the previous four weeks, in whom no pneumococcal vaccine response will be measured in 4-6 weeks: blood samples will be collected at inclusion and a mucosal sample will be collected at a later time point (next outpatient appointment or home visit) when the subject has no antibiotic use in the previous four weeks.

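### Swab dates are not aligned within households and one deferral route has no maximum, so calendar time could confound the carriage comparison if deferral is unequal and enrolment is uneven over the year

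*Protocol*

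**What the plan says.** Objective 1 is to estimate *M. pneumoniae* "carriage in young children with rRTIs and compare this to their family members without infections".

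The protocol's section on timing of sampling gives three routes:

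- No recent antibiotics: "In subjects without antibiotic use in the previous four weeks: all samples, including blood, will be collected at inclusion".
- Recent antibiotics, with a pneumococcal vaccine response due in 4-6 weeks: "all samples, including blood, will be collected when pneumococcal response is measured".
- Recent antibiotics, with no such measurement due: blood is taken at inclusion, and "a mucosal sample will be collected at a later time point (next outpatient appointment or home visit"), once four antibiotic-free weeks have passed.

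The recruitment text for the children also gives only a minimum: "Later sampling (after a period of four weeks without antibiotic use) can occur during a home visit if no further hospital visits are planned".

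The same four-week rule applies to controls: under their exclusion criteria, "a family member can be included but a mucosal sample should be collected four weeks after the last antibiotic course or prophylactic treatment". On when they are recruited, the protocol says: "After the inclusion of a subject with rRTIs, family members will be asked to participate in the study". No passage requires a child and its household controls to be swabbed on the same day or within a set interval.

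On adjustment, the section on statistical analyses says: "Where appropriate, analyses will be corrected for age as a possible confounding variable". It also plans univariable and multivariable logistic regression for carrier status, with models compared by AIC, but lists no covariates.

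**The concern.** Controls from the same household are attractive because they share the child's surroundings and, if swabbed together, the same moment in the circulation of respiratory organisms. Here the moment is set person by person. A child with a recent antibiotic course waits, while a parent or sibling without one is swabbed at their own inclusion.

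The rule is the same for both groups, but its effect may not be. Index children are referred for recurrent infections, and people with recurrent infections are excluded as controls. It is a fair inference that the children have had more antibiotics and are deferred more often. The vaccine-response route probably also concerns mainly the children, who are the ones undergoing immunological screening.

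If carriage rises and falls over the year, a systematic shift in swab date between the groups can then appear as a difference in carriage, or hide one. Age, the one confounder named, would not remove it. Adjustment for season can repair part of this afterwards, but no analysis can make the swabs concurrent.

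**Working it through.** The protocol gives no carriage prevalence, seasonal pattern, share deferred, length of deferral or enrolment calendar, so there is no planned figure to reproduce. The calculation below only shows when a bias arises and how large it could be. All its inputs are assumptions.

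**Model, with no true difference between groups.** With t in months from the carriage peak, p(t) = p̄ × [1 + a × cos(2πt/12)]. A share f of each group is swabbed d months late. Children and controls are assumed to enter on the same calendar.

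- Mean prevalence p̄: 10% or 20%.
- Amplitude a: 0.5 or 0.9.
- Share deferred: 30% of children and 30% of controls; or 30% or 60% of children and 5% of controls.
- Delay d: 1, 1.4 or 3 months.
- Enrolment: uniform over the year; six or three months centred on the peak; or three months on the rise to the peak, centred three months before it.

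With p0 the mean prevalence at enrolment and pd the mean d months later, each group's prevalence is (1 − f) × p0 + f × pd. The apparent odds ratio (OR) compares children with controls.

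For enrolment over W months centred at month c, p0 = p̄ × [1 + a × K × cos(2πc/12)], where K = sin(πW/12)/(πW/12). For pd, replace c by c + d. For W = 3, K = 0.900.

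**One case in full** (p̄ = 20%, a = 0.9, 60% v 5% deferred, d = 1.4, enrolment on the rise, so c = 9):

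- p0 = 0.200, because the cosine is zero at c = 9.
- pd = 0.20 × (1 + 0.9 × 0.900 × sin 42°) = 0.308.
- Children: 0.4 × 0.200 + 0.6 × 0.308 = 0.265.
- Controls: 0.95 × 0.200 + 0.05 × 0.308 = 0.205.
- OR = (0.265/0.735)/(0.205/0.795) = 1.40.

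**Apparent OR when the true OR is 1:**

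| Deferral | Enrolment | Delay 1-1.4 months | Delay 3 months |
|---|---|---|---|
| Any, including 60% v 5% | Uniform over the year | 1.00 | 1.00 |
| Equal (30% v 30%) | Any calendar tried | 1.00 | 1.00 |
| 30% or 60% v 5% | Centred on the peak, 6 or 3 months wide | 0.90-0.99 | 0.66-0.93 |
| 30% or 60% v 5% | 3 months on the rise | 1.06-1.40 | 1.12-1.61 |

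A bias therefore needs unequal deferral and an uneven enrolment calendar together, and it can go either way.

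**These ranges are not bounds.** Enrolment on the fall from the peak is not in the table. With the inputs of the worked case but c = 3, pd = 0.20 × (1 − 0.9 × 0.900 × 0.669) = 0.092. The children's prevalence is 0.4 × 0.200 + 0.6 × 0.092 = 0.135, the controls' is 0.95 × 0.200 + 0.05 × 0.092 = 0.195, and the OR is about 0.65.

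**The case against.** Most of the case against limits the point rather than removing it.

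*The delay need not be long.* A reader might infer that deferral lasts at least four weeks from inclusion. It does not: the four weeks run from the last antibiotic use. A child whose course ended three weeks before inclusion is eligible about one week later. The vaccine-response route is tied to a visit at 4-6 weeks, and a home visit is available when no hospital visit is planned. This stands. A gap of a season is not ruled out, since the remaining route has no maximum and a further antibiotic course restarts the clock, but nothing shows that it is typical.

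*The model may include date.* A reader might infer that sampling date is left out of the analysis. The protocol names only age and leaves the other covariates open, so season is neither named nor excluded, and a statistical analysis plan that is not shown may list it. This stands for the covariate list. It does not answer the timing of swabs, which is a matter for the protocol.

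*The rule is symmetric.* It is, and with equal deferral the calculation shows no bias. Unequal deferral is an inference from the eligibility criteria, without figures.

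*Objective 2 is a separate matter.* It is studied within the children with recurrent infections. Season could confound the relation between microbiota and carriage in any cohort sampled across the year. It would be wrong to attribute that to the deferral rule.

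**Conclusion.** The design point holds in a limited form. The protocol sets no maximum for one deferral route and no sampling interval within households, and age is the only confounder it names. As written, it gives up a match on time that was available at little cost.

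Whether this biases Objective 1 is conditional. It requires carriage that varies with calendar time, more deferral in one group than the other, and enrolment spread unevenly over that variation. If deferral is equal, or enrolment is uniform over the year, the apparent odds ratio is 1.00, and what is lost is comparability within the household. The documents do not support the stronger reading, that calendar variation necessarily shows up as a case-control difference.

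The size cannot be known from the protocol. In the scenarios tabulated, the odds ratio under no true difference ranges from about 0.90 to 1.40 for delays of 1-1.4 months and from about 0.66 to 1.61 for 3 months. It was near 1 in the milder scenarios and moves further away under some calendars that were not tabulated. This is worth correcting because it touches the main comparison and the correction is cheap.

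**What to change.** 1. Where feasible, swab household controls at the visit at which the index child's swab is taken. Home visits are already provided for as a fallback and could serve. State the intended interval between swabs in a household and a latest time for the deferred swab.
2. Record the date of every swab. Include season and year of swab alongside age in the carriage models as specified terms, not left to selection by AIC. Include them in the microbiota models too, as a general confounder that does not arise from the deferral rule.
3. Repeat Objective 1 in households whose swabs were taken within a stated interval, for example two weeks. Report the share deferred and the distribution of swab dates by group, which would show whether the conditions for bias are met.

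If collection is complete, items 2 and 3 can still be done, provided that swab dates were kept.

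Cost: some coordination of visits. Some control swabs would be taken later than the present rule has them, and some controls may need antibiotics in the interval. The extra covariates use a few degrees of freedom, and the restricted analysis has fewer households.
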